### Outcome measures

The primary outcomes include proportion preterm birth (ultrasound-confirmed gestational age at birth < 37 completed weeks); proportion SGA (birth weight centile <10th as per INTERGROWTH-21 standard) on day 7 of birth; proportion LBW (birth weight < 2500 g); mean birth weight and length; attained length (LAZ) at 24 months of age and proportion stunted (LAZ < -2 SD).

The list of secondary outcomes along with the timing of measurements during the pre- and peri-conception, pregnancy and postnatal periods are provided in Additional file 3.

The key secondary outcomes for children are proportion stunted at 6 and 12 months, wasted and underweight at 6, 12 and 24 months, weight and length trajectories from birth to 24 months, body composition (in a subsample) at 1 month of age and neurodevelopment at 6, 12, 18 and 24 months (in a subsample), micronutrients and anemia status at 24 months, morbidity and hospitalization from birth to 24 months (Additional file 3).

The key secondary outcomes for women are micronutrients and anemia status, depressive symptoms and infection at the end of pre- and peri-conception, during pregnancy and postpartum period (Additional file 3).

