#### Outcome ascertainment

Participants in both groups are visited by the independent outcome ascertainment team at the end of pre- and peri-conception period. The symptoms of RTI, depressive symptoms, compliance to interventions, micronutrient, anemia, thyroid and diabetes status are ascertained. During pregnancy, weight gain, compliance to interventions and micronutrient status is assessed. Weight, length, head- and mid-upper arm circumference, child care practices, prevalence of illness and care seeking and hospitalization are assessed during early childhood (Additional file 3).

Weights and lengths are taken by pair of workers using digital weighing scale (model 354; Seca, California, USA) and infantometer (model 417; Seca, California, USA) to the nearest 10 g and 0.1 cm, respectively. Head and mid-upper arm circumference is taken using a measuring tape (model 212; Seca, California, USA) [66–68].

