#### Laboratory investigations

At enrolment, ~ 10 ml blood sample is obtained from women in the intervention group to screen for anemia, thyroid disorders, diabetes, RPR and micronutrient assays. Around 10 ml blood is taken from women in both intervention and control groups when they report pregnancy or do not get pregnant during 18 months of the pre- and peri-conception period, in the third trimester of pregnancy and at 6 months postpartum from women in the intervention and control groups for anemia assessment, micronutrient status and inflammatory markers. 5 ml blood will be collected from children at 24 months of age in both groups for micronutrient assays.

The samples are centrifuged and serum is stored in a − 80 °C deep freezer in the “Clinical and Research Laboratory” set up in the field office, which is accessible only to the laboratory managers. Laboratory investigations are done in an accredited commercial laboratory (Strand-Quest Diagnostics Laboratory) and at referral hospitals (Safdarjung Hospital). The body composition analysis will be done by isotope dilution technique using deuterium oxide (2H2O) at 1 month of age in a subsample [69]. The infant saliva samples will be analyzed for enrichment of deuterium by Fourier transform infrared (FTIR) spectrophotometry [69].

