#### Comparability between the two groups

Summary values (means, proportions) for sociodemographic characteristics among the groups will be presented in the baseline table. We will not perform any test of significance. Our large sample size is likely to yield a balance between the groups. However, we will carefully examine the size of any baseline differences. Imbalanced characteristics that may influence the primary outcomes will be adjusted appropriately.

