#### Main effects

Analysis will be done by intention-to-treat. Mean (SD) birth weight, birth length, LAZ score at 24 months, proportion of preterm birth and spontaneous preterm birth, SGA, LBW, stunting at birth and 24 months will be presented for the different groups.

For binary outcomes, generalized linear models (GLMs) of the binomial family with a log-link function will be used to calculate the effect size [relative risk and 95% confidence interval (CI)]. For continuous outcomes, GLMs of the Gaussian family with an identity-link function will be used to calculate the effect size (difference in means and 95% CIs). The effect of interventions on secondary outcomes will be assessed using the same models as for primary outcomes.

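### For A+C vs B+D on women's later haemoglobin and micronutrients, the stated models name no early-pregnancy value as a covariate, although blood is taken in both groups at pregnancy report; adding it would gain precision

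*Protocol article*

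**What the plan says.** Under Outcome measures, "The key secondary outcomes for women are micronutrients and anemia status, depressive symptoms and infection", assessed at the end of the pre-conception phase, in pregnancy and postpartum.

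Laboratory investigations gives the blood schedule. "Around 10 ml blood is taken from women in both intervention and control groups when they report pregnancy", and blood is drawn again "in the third trimester of pregnancy and at 6 months postpartum from women in the intervention and control groups for anemia assessment", with micronutrient assays at the same points. Enrolment blood, by contrast, is described for the intervention group only.

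Outcome ascertainment adds that "Participants in both groups are visited by the independent outcome ascertainment team at the end of pre- and peri-conception period".

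Main effects sets a log-link binomial model for binary outcomes. For the rest, "For continuous outcomes, GLMs of the Gaussian family with an identity-link function will be used to calculate the effect size". It then says "The effect of interventions on secondary outcomes will be assessed using the same models as for primary outcomes", and Pre-specified subgroup analysis repeats this. No covariate is listed.

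The only adjustment rule for these models is under Comparability between the two groups: "Imbalanced characteristics that may influence the primary outcomes will be adjusted appropriately".

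**The concern.** The primary outcomes (birth size, preterm birth, SGA, LBW, length at 24 months) cannot have a pre-randomisation value of the same quantity, so a model without one is natural for them. Applied unchanged to women's haemoglobin and micronutrients, the same model leaves out a value that the trial already collects in every arm and that probably predicts the later one.

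What is at stake is the precision of the antenatal/postnatal package effect on women's nutritional status, which is part of the secondary objective. The two-stage design is a further reason to write the rule down. The pregnancy-report value is a legitimate covariate for the second randomisation but an outcome of the first, so a general instruction to adjust for baseline could be misapplied.

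**Working it through.** **Order of events.** Study design, Randomization, and the section on the period after the second randomisation give the same sequence: pregnancy reported, scan at 9 to 13 weeks, rescreening, consent, second randomisation. Blood is drawn when pregnancy is reported, so it naturally falls before the second allocation. The article does not say so outright.

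**Which comparison.** For A+C vs B+D the value precedes allocation. For A+B vs C+D, and for A vs D (arms that also differ in the first package), it comes after the first randomisation and may carry part of that package's effect.

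**The plan's own figure first.** Table 1: 0.15 SD, 90% power, two-sided 5%.

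n = 2 × (1.960 + 1.282)² / 0.15² = 934, against 935 stated. This reproduces as an unadjusted comparison of two means.

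**Expected women per side of A+C vs B+D** (Sample size section):
- Pregnancies: 13,500 × 0.45 = 6,075.
- Live births: 6,075 × 0.70 = 4,252.5, or about 2,126 per side.
- At 24 months: 4,252.5 × 0.80 = 3,402, or 1,701 per side. I use this as a lower bound for the 6-month postpartum sample.

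**Gain from the covariate.** For a continuous outcome with correlation ρ between the early and later value, residual variance is multiplied by (1 − ρ²) and the standard error by √(1 − ρ²). The article gives no ρ, so 0.3 to 0.7 is an assumed range.

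| ρ | SE ratio | Interval narrower by | Sample equivalent, 1/(1 − ρ²) |
|---|---|---|---|
| 0.3 | 0.954 | 4.6% | 1.10 |
| 0.5 | 0.866 | 13.4% | 1.33 |
| 0.7 | 0.714 | 28.6% | 1.96 |

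**Power.** Φ(d√(n/2)/√(1 − ρ²) − 1.96), with d = 0.10 SD:

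| n per side | Unadjusted | ρ = 0.3 | ρ = 0.5 | ρ = 0.7 |
|---|---|---|---|---|
| 1,701 | 83.1% | 86.4% | 92.0% | 98.3% |
| 2,126 | 90.3% | 92.8% | 96.4% | 99.5% |

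The 0.10 SD is borrowed from the Background, where it is the effect of a single intervention on birth weight and attained length. It is not a haemoglobin effect.

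At d = 0.15 SD, the size assumed for each package in Table 1, unadjusted power is 99.2% at 1,701 per side and 99.8% at 2,126. There the gain is only a narrower interval.

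**Binary anaemia status.** The (1 − ρ²) factor does not carry over to a log-binomial risk ratio. I have not quantified that gain; it is likely smaller.

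**The case against.** The strongest objection is that this rests on silence. Main effects fixes the family, link and effect measure. It does not say that the models are unadjusted, and a covariate list is commonly left to the full protocol or SAP, neither of which is shown. That stands to this extent: a reader might infer that the plan ignores or excludes early-pregnancy values, and the text does not support that; it simply names none. What remains is that the article states the secondary-outcome model twice by reference to outcomes without a baseline. Its section on growth trajectories, by contrast, brings covariates in explicitly.

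Second, the imbalance rule might reach these values. The Discussion lists maternal anaemia and undernutrition among risk factors for poor outcomes, so a large imbalance could trigger adjustment. This is fair, but the rule depends on imbalance, refers to the primary outcomes and follows a sociodemographic baseline table. It does not provide for adjustment because a value is prognostic. Chance imbalance is also small here: its standard error is √(2/2,126) ≈ 0.03 SD.

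Third, it is tempting to call these values true pre-randomisation baselines. The blood draw is not explicitly placed before allocation, so only samples dated before it qualify.

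Fourth, one might extend the point to depressive symptoms. At the end of the pre-conception phase, "The symptoms of RTI, depressive symptoms, compliance to interventions, micronutrient, anemia, thyroid and diabetes status are ascertained", but the list for pregnancy in the same section omits depressive symptoms. The repeated screening in pregnancy is described under intervention delivery, and Additional file 3 is not shown. The article does not establish measurement in all arms on both sides of the second randomisation.

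Finally, an unadjusted randomised comparison is valid. That stands in full.

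**Conclusion.** The point holds as a modest efficiency improvement for haemoglobin and micronutrients in A+C vs B+D. Intervals for continuous outcomes would be about 5% to 29% narrower across assumed correlations of 0.3 to 0.7. The direction is certain for any non-zero correlation; the size cannot be fixed from the article.

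A reader might infer that the unadjusted comparison is biased or underpowered. Neither follows. Randomisation protects the estimate, and at 0.15 SD with the expected sample unadjusted power exceeds 99%. Power improves materially only for effects of about 0.10 SD or less. The conclusion assumes that the pregnancy-report sample precedes the second allocation for most women. It is a desirable refinement, not a necessary correction.

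**What to change.** Add to Main effects, or to the SAP:

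- For women's haemoglobin and micronutrient outcomes measured after the second randomisation, the A+C vs B+D model includes the woman's own value of the same measure, using only samples dated before the second allocation, and an indicator for the first package.
- This value is not used in the A+B vs C+D or A vs D models, because it is measured after the first randomisation.
- Depressive symptoms are treated in the same way only if they are measured in all arms both before and after the second randomisation.

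The cost is a few lines of wording and a covariate already being collected. Two details need settling in advance: a simple way to keep women without a usable early-pregnancy value in the model, and a fallback if the adjusted log-binomial model for anaemia status does not converge.

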#### Weight and length growth trajectories between birth and 24 months

A multivariable linear mixed-effect regression model with an unstructured covariance matrix will be used to examine the effect of the interventions on weight and length trajectories from birth to 24 months [73]. In this model, in order to account for the interdependence of multiple observation periods in the same child, time (age in months) of assessment will be taken to be the level-1 source of variation, with individual children at level 2. All potential covariates will be included as fixed effect variables in this model. The interaction between maternal stature and time (age in months) of assessment on different anthropometric outcomes i.e. LAZ, WAZ (weight-for-age z-score) and WLZ scores will be examined. If significant, the interaction term will be included in the model to obtain the independent effect of maternal stature at different ages.

#### Pre-specified subgroup analysis

We will conduct subgroup analysis for women according to their height (< 150 cm and ≥ 150 cm), underweight, BMI status at enrolment and at the time of pregnancy confirmation, years of education and high risk pregnancy. We will also conduct subgroup analysis by wealth quintile of the household. The relative measures of effect within each of these subgroups will be estimated.

The effect of interventions on secondary outcomes will be assessed using the same models as for primary outcomes.

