### Objectives

The primary objective is to determine the effect of integrated and concurrent delivery of interventions to improve health, nutrition, WASH and psychosocial status during the pre- and peri-conception period alone (pre- and peri-conception intervention package); during pregnancy and early childhood (enhanced antenatal, postnatal and early childhood care) and; throughout the pre- and peri-conception period, pregnancy and early childhood (pre- and peri-conception intervention package and enhanced antenatal, postnatal and early childhood care), on preterm birth, LBW and SGA, and stunting at 24 months of age compared to routine care and additionally, to assess whether the effect of these interventions differs by maternal stature (< 150 cm or ≥ 150 cm).

The secondary objectives are to determine the effect of the same package on nutritional status, morbidity and neurodevelopment in children, and on women’s nutritional status and morbidity in the pre- and peri-conception, pregnancy and postpartum periods.

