We propose to enrol a total of 13,500 eligible women (6750 in pre- and peri-conception intervention package group and 6750 in control group) based on the following assumptions: 45% of reproductive-age women randomized get pregnant in the 18 months of the pre- and peri-conception intervention period, 30% loss (abortions, still births, maternal deaths, moving away, refusals) between pregnancy and live birth and 20% loss (loss-to-follow-up and child deaths) between birth and 24 months of age.

We will get ~ 1100 live births per group. This will enable us to detect a 25% difference in preterm births, proportion LBW and SGA between pre- and peri-conception package alone and control group (A + B vs C + D) and enhanced antenatal, postnatal and early childhood care alone and control group (A + C vs B + D) and a mean difference of 0.15 SD in LAZ score at 24 months for the above comparisons.

We will get at least 600 children in each of the four groups (A, B, C, D) at 24 months. We will be able to detect 0.2 SD difference in mean LAZ score at 24 months and 0.2 SD difference in birth weight and birth length between pre- and peri-conception intervention package and enhanced antenatal, postnatal and early childhood care and control group.

The sample size of ~ 2400 (at least 600 children in each of the 4 groups) at 24 months of age will also allow us to detect an interaction odds ratio (lOR) of ≥1.70 to 1.85 in the proportion of stunted children among short mothers (< 150 cm) and among tall mothers (≥ 150 cm) between the control (routine care) and the intervention group who received the intervention package throughout, with 80% power and 95% confidence level.

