### Study procedures

#### Screening and enrollment

The screening and enrolment team (SET) identify eligible women through a door-to-door survey in the study areas of Dakshinpuri, Govindpuri, Madangir and Tigri, Khanpur, Sangam Vihar, Jaitpur and Meethapur and Madanpur Khadar areas of South Delhi. Information about the study is shared with families and written informed consent is taken from those who meet the inclusion criteria and are willing to participate in the study. Height (Seca-213 stadiometer) and weight (Salter 9509 weighing scale) measurements are taken and the participant is allocated to the intervention (pre- and peri-conception) or control (routine care) group [56, 57]. The intervention delivery team is informed if the woman is randomized to the intervention group.

Post-enrolment, information is documented on sociodemographic characteristics and the enrolled woman is requested to inform the study team by calling designated phone numbers if she gets pregnant. Workers from the SET make calls to all women every month (or home visits if the call is unsuccessful) to enquire about missed periods. If women report two missed periods or inform that they are pregnant (self-testing using a pregnancy kit), a trans-abdominal ultrasound is scheduled.

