### Randomization, allocation and masking

The randomization list was prepared by an independent statistician at World Health Organization (WHO) using random permuted blocks, stratified by maternal height [< 150 cm (< − 2 SD) and ≥ 150 cm (≥ − 2 SD)] of the WHO standards [58].

The first randomization is done at enrollment when married women aged 18 to 30 years fulfil the eligibility criteria and consent to participate in the study. The second randomization is done when women become pregnant during the 18 months follow up period, and are eligible (not moving away from the study area) at rescreening and consent to their own and their baby’s participation in the study. The group allocation is done through a web-based system. There are no additional criteria for discontinuation or modification of allocated interventions.

Masking participants and study teams is not possible because of the nature of interventions in this trial. However, attempts are made to keep the independent outcome ascertainment team unaware of the group allocation, to the extent possible.

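### The only stated analysis of effect modification by maternal stature, part of the primary objective, is a split at 150 cm; a package-by-height interaction in centimetres should be added beside it

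*Protocol article*

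**What the plan says.** All references are to the protocol article.

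- **Objectives.** Stature modification belongs to the primary objective, and the classes are written into it: "to assess whether the effect of these interventions differs by maternal stature (< 150 cm or ≥ 150 cm".
- **Pre-specified subgroup analysis.** "We will conduct subgroup analysis for women according to their height (< 150 cm and ≥ 150 cm", and then "The relative measures of effect within each of these subgroups will be estimated".
- **Sample size.** The trial is said to be able to "detect an interaction odds ratio (lOR) of ≥1.70 to 1.85 in the proportion of stunted children among short mothers (< 150 cm" compared with tall mothers. The contrast is "between the control (routine care) and the intervention group who received the intervention package throughout", "with 80% power and 95% confidence level".
- **Randomization, allocation and masking.** The list was made "using random permuted blocks, stratified by maternal height", at the same 150 cm cut, which is described there as -2 SD of the WHO standards.
- **Screening and enrollment.** "Height (Seca-213 stadiometer) and weight (Salter 9509 weighing scale) measurements are taken and the participant is allocated". Height is therefore recorded on its natural scale before treatment is assigned.
- **Weight and length growth trajectories.** Stature appears here only in an interaction with time. That describes how growth differs by stature, not how a package effect differs by stature.

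The article gives neither the share of women below 150 cm nor the mean or SD of height. It states no package-by-height analysis on the continuous scale.

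**The concern.** A two-class modifier treats women of 138 cm and 149.5 cm as alike, and women of 149.5 cm and 150.5 cm as different. If the package effect drifts smoothly with height, most of that drift lies within the classes and the split cannot see it.

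This matters more here than for an ordinary subgroup. The stature question sits in the primary objective. The Discussion presents the role of maternal height as something the design makes answerable, and lists intergenerational effects as the third strength of the study. Interaction tests are weak to begin with. A null result from an inefficient test could be read as evidence that stature does not alter the effect of the packages, when the test had little chance of showing that it does.

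**Working it through.** **1. The plan's own interaction figure.** Inputs from Sample size: at least 600 children per group, 30% stunting, 80% power, 95% confidence, combined package (A) against routine care (D). Assumed, because not given: the share short, 30% stunting in both height classes under routine care, and no effect in tall mothers.

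Var(log interaction OR) = sum over the four arm-by-height cells of 1/[n p (1-p)]. The detectable value solves log(OR)/sqrt(Var) = 1.96 + 0.84 = 2.80.

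Example with 20% short (120 short and 480 tall per arm) and OR 2.35:
- Stunting among short mothers in A: odds 0.4286 x 2.35 = 1.007, so p = 0.502.
- Var = 1/(120 x 0.21) + 1/(120 x 0.25) + 2/(480 x 0.21) = 0.0397 + 0.0333 + 0.0198 = 0.0929.
- log(2.35)/sqrt(0.0929) = 0.854/0.305 = 2.80.

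| Share < 150 cm | 600 per arm | 850 per arm* | 1200 per arm |
|---|---|---|---|
| 20% | 2.35 | 2.05 | 1.83 |
| 30% | 2.11 | 1.88 | 1.70 |
| 50% | 2.00 | 1.79 | 1.63 |

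*13,500 x 0.45 x 0.70 x 0.80 / 4 = 850, from the article's own loss assumptions.

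Varying stunting from 27% to 50% and the share short from 10% to 50%, the smallest two-sided value at 600 per arm is 1.93. The stated 1.70 to 1.85 is therefore not reproduced for A against D at 600 per group. It does fit all of the roughly 2400 children compared 1200 with 1200 at 20-30% short. At 600 per arm, power for 1.70 to 1.85 is 41-52% with 20% short and 51-63% with 30% short. Which contrast that figure describes is a separate matter. Here it shows only that the split interaction has little precision to spare.

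**2. Information kept by the split.** Assume normal height, an effect linear in height, and roughly constant information per woman across heights. With p the share below 150 cm and z its normal quantile, the split keeps the squared correlation between height and its indicator:

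E = phi(z)^2 / [p(1-p)]

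- p = 0.20: 0.280^2/0.16 = 0.490, loss 51%
- p = 0.35: 0.370^2/0.2275 = 0.603, loss 40%
- p = 0.50: 0.399^2/0.25 = 0.637, loss 36%
- Outside that range: p = 0.15 gives 0.426 (loss 57%), and p = 0.10 gives 0.342 (loss 66%)

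**3. In terms of power.** If continuous height has 80% power, the split has Phi(2.80 x sqrt(E) - 1.96):

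- p = 0.20: Phi(0.00) = 50%
- p = 0.35: Phi(0.22) = 58.5%
- p = 0.50: Phi(0.28) = 61%

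As a sample-size ratio this is 1/0.637 = 1.6 to 1/0.490 = 2.0.

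**4. The reverse case.** The correlation in step 2 is symmetric. If the truth is a step at 150 cm, the split is the correct model and the linear term keeps only E. A simulated interaction model with 1200 children (A + D) confirms both directions:

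| Share short | Truth | Continuous | Split |
|---|---|---|---|
| 20% | linear | 80% | 49% |
| 20% | step | 49% | 81% |
| 50% | linear | 79% | 61% |
| 50% | step | 61% | 81% |

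**The case against.** The strongest reply is that the split is the question the trial asks. The objective, the randomisation strata, the power statement and the subgroup analysis all use 150 cm. The cut is external (-2 SD of the WHO standards) and was not chosen from the data. For a contrast between two classes, the two-class analysis discards nothing, and a slope per centimetre is a different estimand. This stands, and it is why the 150 cm contrast should keep its place.

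Three further points also stand:
- Under a threshold the advantage reverses, as step 4 shows. A spline check may reveal the misfit but does not give the linear test its power back.
- Most of the primary outcomes are binary and are to be fitted with log-binomial models. There the information varies with risk, so the efficiency formula is only approximate, and a continuous interaction may fail to converge.
- The statistical analysis plan is not shown and could contain such a model.

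What the reply does not settle is that the article offers no reason to expect a biological threshold at 150 cm, while the Discussion speaks of maternal height in general. Stratifying at a cut does not confine the analysis to that cut. With the functional form unknown, relying on either form alone is a gamble that data already collected make unnecessary.

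**Conclusion.** The point holds as a cheap improvement to a question in the primary objective, not as a mistake in the plan. The only stated analysis of package effect by stature is the 150 cm split, although height is measured before allocation. The loss is about 36-51% of the information, or 50-61% power in place of 80%. It is conditional on roughly normal height, modification about linear in height, and 20-50% of women below 150 cm. With 10-15% short the loss would be 57-66%. With a step at 150 cm there is no loss and the split is the better test.

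Three stronger readings are tempting and are not supported:
- That the trial certainly discards a third to a half of its information on stature. The share short, the height distribution and the form of modification are all absent from the article.
- That the split serves no purpose and should become a mere descriptive display. It answers the objective as written, matches the strata, and wins under a threshold.
- That BMI and years of education suffer the same loss. The subgroup section states no cuts for either.

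**What to change.** Keep the < 150 / ≥ 150 cm contrast as the prespecified answer to the objective as written, matching the randomisation strata. Beside it, prespecify for each primary outcome a package x height interaction with height in centimetres, linear, with a spline check of the form. Report the estimated package effect with its confidence interval at about 145, 150 and 155 cm. State in advance how the two results will be read together, so that neither can be picked after the fact.

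The change needs a short addition to the analysis text and no new data. Its costs are a second test of the same question, a result that depends on the assumed functional form, and possible convergence failure of the log-binomial models with a continuous interaction, for which a fallback model should be named.
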